## Abstract

**Background:**

Erosive lichen planus affecting the vulva (ELPV) is a relatively rare, chronic condition causing painful raw areas in the vulvovaginal region. Symptoms are pain and burning, which impact upon daily living. There is paucity of evidence regarding therapy. A 2012 Cochrane systematic review found no randomised controlled trials (RCTs) in this field. Topically administered corticosteroids are the accepted first-line therapy: however, there is uncertainty as to which second-line treatments to use. Several systemic agents have been clinically noted to show promise for ELPV refractory to topically administered corticosteroids but there is no RCT evidence to support these. The ‘hELP’ study is a RCT with an internal pilot phase designed to provide high-quality evidence.

**Methods/Design:**

The objective is to test whether systemic therapy in addition to standard topical therapy is a beneficial second-line treatment for ELPV. Adjunctive systemic therapies used are hydroxychloroquine, methotrexate, mycophenolate mofetil and prednisolone. Topical therapy plus a short course of prednisolone given orally is considered the comparator intervention. The trial is a four-armed, open-label, pragmatic RCT which uses a blinded independent clinical assessor. To provide 80 % power for each comparison, 96 participants are required in total. The pilot phase aims to recruit 40 participants.

The primary clinical outcome is the proportion of patients achieving treatment success at 6 months. ‘Success’ is defined by a composite measure of Patient Global Assessment score of 0 or 1 on a 4-point scale plus improvement from baseline on clinical photographs scored by a clinician blinded to treatment allocation. Secondary clinical outcomes include 6-month assessment of: (1) Reduction in pain/soreness; (2) Global assessment of disease; (3) Response at other affected mucosal sites; (4) Hospital Anxiety and Depression Scale scores; (5) Sexual function; (6) Health-related quality of life using ‘Short Form 36’ and ‘Skindex-29’ questionnaires; (7) Days of topical steroid use; (8) Treatment satisfaction; (9) Discontinuation of medications due to treatment failure; (10) Per participant cost of intervention in each treatment group. Adverse events will also be reported.

**Discussion:**

‘hELP’ is the first RCT to address second-line treatment of ELPV. The trial has encountered unique methodological challenges and has required collaborative efforts of the UK Dermatology Clinical Trials Network alongside expert clinicians.

**Trial registration: current controlled trials:**

ISRCTN 81883379. Date of registration 12 June 2014.

**Electronic supplementary material:**

The online version of this article (doi:10.1186/s13063-015-1133-z) contains supplementary material, which is available to authorized users.

## Background

Erosive lichen planus is a chronic inflammatory, scarring skin condition that most commonly occurs on the mucosal surfaces of the mouth and genital region. It is believed to be an autoimmune condition [1, 2] with T-cell-mediated damage to keratinocytes in the basal layer of the epidermis [3], although the exact pathogenesis remains unclear.

Erosive lichen planus affecting the vulvovaginal region (ELPV) causes painful raw areas at the vaginal entrance, and subsequent scarring leads to anatomical changes with narrowing of the vaginal canal. Symptoms can prevent normal daily activities such as walking/sitting, washing, going to the toilet and normal sexual function. Additionally, there is a 1–3 % risk of cancerous change in affected skin although the timescale for malignancy to occur is unclear [4–6].

ELPV is estimated to affect 0.01 % of women. However, this is likely an underestimate with many cases failing to present to medical services [7].

No robust, high-quality randomised controlled trials (RCTs) have been published on which to base treatment decisions for ELPV [8]. First-line therapy is typically with the super-potent topical steroid clobetasol propionate 0.05 % [9, 10]. Non-randomised studies, mainly retrospective case series, have suggested that clobetasol propionate is an appropriate first-line therapy [6, 11–13]. However, in the only prospectively-collected case series [6], one third of patients responded poorly to this type of treatment.

There is currently no agreement as to which second-line agents should be used [10, 14]. Therapeutic choice is based upon expert opinion and predominantly includes immunosuppressant or immune-modifying agents.

Expert clinicians anecdotally believe that systemic treatments with the greatest success rates are hydroxychloroquine, methotrexate, mycophenolate mofetil and prednisolone. In a UK-based multi-centre case note review of 172 patients, these were the most commonly prescribed systemic agents [9]. However, there are insufficient data within the medical literature to make an evidence-based decision on the most effective. The ‘hELP’ trial (Systemic therapy for vulval Erosive Lichen Planus) has been designed to test all four of the more common interventions in one four-armed RCT with an internal pilot.

The objectives of the ‘hELP’ study are to administer, for a 6-month period, in patients with ELPV that has been refractory to first-line therapy, clobetasol propionate 0.05 % topically plus adjuvant systemic therapy with hydroxychloroquine, methotrexate or mycophenolate mofetil, and compare against topically administered clobetasol propionate 0.05 % with adjuvant prednisolone given orally.

## Methods/Design

### Study design

The ‘hELP’ trial is a multi-centre, four-armed, open-label pragmatic RCT. The trial has a 12-month internal pilot phase. Participants are being recruited from 12 hospitals throughout the UK which hold specialist vulval clinics. The active intervention phase is for 6 months after which the primary outcome will be assessed. Participants will be followed up for 12 months after randomisation. Treatment regimens and monitoring are based upon national guidance issued by the British Association of Dermatologists [15]. Study visits mimic the schedule of clinic appointments seen in usual clinical practice, the timings of which were set following consultation with expert clinicians.

### Participants

Inclusion criteria arei).Aged 18 or over;ii).Clinical diagnosis of moderate to severe ELPV, despite first-line therapy for 3 months with clobetasol propionate 0.05 %;iii).A documented vulval biopsy at some point in their history to exclude malignant/pre-malignant disease. The biopsy should be repeated if clinical features have changed or are suspicious;iv).Willing to have clinical photographs taken;v).If of childbearing potential, willing to use effective contraceptive methods whilst taking systemic therapy (and in the case of methotrexate for 6 months after the end of treatment);vi).Willing to give informed consent.

Participants are ineligible if they have:i).Lichen sclerosus/lichen planus overlap syndrome;ii).Received one or more of the trial drugs within the last month (excluding topical therapy);iii).A previous or current diagnosis of malignant disease;iv).Pre-malignant cervical or vulval disease;v).Received a live vaccine in the 2 weeks before starting trial treatment;vi).Pregnancy or are breast-feeding;vii).Known allergy to any of the trial medications;viii).Previous history of clinically significant renal or liver impairment, or concurrent medications that would interact with the trial drugs;ix).Any other reason that the trial drugs would not be given in usual clinical practice.

### Interventions

All participants receive standard topical therapy of clobetasol propionate 0.05 % once daily for 1 month and the regimen will be reduced according to response thereafter. If the condition worsens, application may be increased, but as ELPV is a relapsing remitting condition, this does not necessarily indicate treatment failure. A maximum of 60 g clobetasol propionate 0.05 % over 6 months should be used.

Participants will be randomised to receive one of four systemic treatments (in addition to topical therapy) for a period of 6 months. The 4-week course of prednisolone given orally will be considered the comparator intervention.

Topical therapy alone would have been a simpler comparator, but we considered it unethical to continue this alone as, by definition to enter the trial, topical therapy must have failed. Therefore, a short course of prednisolone given orally for the first month is given to the comparator group.

#### Intervention regimens

Prednisolone given orally starting at 20 mg once daily for 1 week, reducing by 5 mg per week for 4 weeks. Where clinically indicated, gastric and bone protection should be prescribed according to usual practice.Oral hydroxychloroquine tablets up to 6.5 mg/kg body weight with a maximum dose of 200 mg twice daily.Oral methotrexate tablets commencing at 5 mg/week and gradually titrated according to response to a maximum of 25 mg/week.Oral mycophenolate mofetil tablets commencing at 500 mg once daily and gradually titrated according to response to a maximum dose of 1.5 g twice daily.

Treating clinicians are advised to titrate the dose of the active interventions, according to response and tolerability, as detailed in national guidelines issued by the British Association of Dermatologists [15]. As methotrexate is a folate antagonist it is recommended that participants are prescribed adjunctive folic acid 5 mg daily except on the day of methotrexate administration. Clinicians are allowed to use their clinical judgement to deviate from these recommendations if clinically necessary.

Participants in the RCT should not use any other topical or systemic treatments for ELPV after randomisation. There is a 4-week washout period of any pre-existing therapy with the exception of clobetasol propionate 0.05 %. All other concomitant medications should continue as per normal care. The use of live vaccines is not permitted during the intervention phase of the trial and the prescription of any additional medications for ELPV during the trial period is considered as a treatment failure.

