### Clinical outcomes

#### Primary clinical outcome measure

The primary outcome of the ‘hELP’ study is the *proportion of patients achieving treatment success at 6 months*. Treatment will be classed as successful if *both* patient and investigator success criteria are met:Patient Global Assessment of disease severity of ‘none’ or ‘mild’ (on a 4-point scale of none, mild, moderate or severe disease)Any improvement from baseline judged by blinded assessment of clinical photographs

The composite outcome incorporates both blinded assessment of physical signs, where blinding is important in open-label trials, and patient assessment of symptoms, which is important because physical signs do not always reflect symptoms.

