**Fig. 1 Fig1:**
[figure not shown]
Systemic therapy for vulval Erosive Lichen Planus (‘hELP’) study flow diagram. Internal pilot phase to run for 12 months, after which recruitment rates will be assessed and a decision made whether or not to continue onto a definitive trial

After the 6-month visit normal care will resume; the trial medication will continue if adequate control has been achieved, otherwise an alternative approach will be chosen by the treating clinician. No further in-person trial visits will be required: however, participants will be contacted by phone or Email at 12 months by the coordinating centre to assess long-term outcomes.

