### Statistical analysis

If fewer than 40 participants in 12 months are recruited, feasibility outcomes will be reported. Summary data for efficacy outcomes will still be reported in full for potential inclusion in future meta-analyses. However, significance testing and multiple imputation of missing data will not be considered.

All analyses will be performed using the intention-to-treat principle. The ‘Full Analysis Set’ will be all participants who are randomised and continue to be eligible after the post-randomisation eligibility assessments to their allocated trial arm regardless of whether they commence the study medication, or not. All primary and secondary outcome measures will be analysed using this sample of patients.

The primary clinical outcome measure will also be assessed on a per-protocol sample which includes all participants in the ‘Full Analysis Set’ who are deemed to have no major protocol violations that could interfere with the objectives of the study: for example, continuing concomitant medications that are contraindicated in conjunction with the trial treatments.

The primary clinical outcome is a composite measure comprising assessment of digital photographs and Patient Global Assessment. If digital photographs are not available for any of the participants, the assessment that has been recorded by the treating clinician as part of data collection at each trial visit will be used instead. However, if used, this assessment will be unblinded due to the open-label nature of the trial.

Multiple imputation will be used to deal with missing patient assessments or investigator assessments. Fifty imputations will be used to generate 50 complete datasets. The relevant outcome in each dataset will be analysed using the corresponding methods described above with the results across datasets combined using Rubin’s rules. Imputations will be done separately within treatment groups.

Statistical tests will be at the 2-sided 0.05 level, apart from the analysis of the primary clinical outcome measure, which will adjust for multiple comparisons using Dunnett’s step-down procedure [18] to control the familywise error rate at the 0.05 level. All analyses will be adjusted for the minimisation variables and, if applicable, the baseline measurement of the corresponding outcome.

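### The failure rule for additional ELPV medication is not carried into the primary outcome definition or the imputation rule, so the same woman can be coded as a failure or a success

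*Protocol article*

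**What the plan says.** Three sections of the protocol article bear on how a woman who receives another ELPV drug is counted.

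- **Intervention regimens.** "Participants in the RCT should not use any other topical or systemic treatments for ELPV after randomisation". The same paragraph adds that "the prescription of any additional medications for ELPV during the trial period is considered as a treatment failure".
- **Primary clinical outcome measure.** Success at 6 months requires that both "patient and investigator success criteria are met". The first is "Patient Global Assessment of disease severity of ‘none’ or ‘mild" and the second is "Any improvement from baseline judged by blinded assessment of clinical photographs". No condition on additional medication appears. The abstract gives the same two components, and the Discussion also requires only patient and investigator improvement.
- **Statistical analysis.** "Multiple imputation will be used to deal with missing patient assessments or investigator assessments". Imputation is done separately within treatment groups. If photographs are unavailable, the treating clinician's assessment is substituted. No exception is made for women who already count as failures under Intervention regimens. The full analysis set keeps randomised women who remain eligible, whether or not they start the allocated drug.

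**The concern.** Intervention regimens labels a participant a failure because of what was prescribed. The outcome section labels her a success because of how she responded. The full analysis set has no exclusion for additional prescribing, so she stays in the primary analysis and must receive one code. The article does not say which rule takes precedence.

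The choice may not fall evenly across arms. Comparator systemic treatment is a 4-week prednisolone course, and the Discussion expects disease control at 6 months in that arm to match topical therapy alone, which had already failed at entry. Additional prescribing is therefore plausibly more common in the comparator, although the article gives no figures. Prescribing decisions are made by clinicians who know the allocation. If comparator women who respond to an added drug are credited as comparator successes, the difference in proportions shrinks. If they are coded as failures, it does not. The coding should be fixed before anyone sees the unblinded data.

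**Working it through.** **1. The sections side by side.** Take a woman prescribed another ELPV drug at month 4.

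| Her 6-month data | Intervention regimens | Outcome and analysis sections, read literally |
|---|---|---|
| Both criteria met | Failure | Success |
| One or both criteria not met | Failure | Failure |
| Assessment(s) missing | Failure | Missing component(s) imputed within her arm; may become success |

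The rules disagree in the first row and can disagree in the third. They agree in the second, so the conflict is confined to women with additional medication who respond or are unobserved.

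**2. The plan's own sample size.** Inputs from Sample size and recruitment: 10% v 50% success, 1:1:1:1 allocation, 96 in total (24 per arm), 80% power, two-sided familywise error 5%. The Statistical analysis section specifies Dunnett's step-down procedure. For three comparisons with a shared comparator (correlation 0.5, large sample), the two-sided Dunnett critical value is 2.349, or 0.0188 per comparison.

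Arcsine effect size: h = 2·arcsin√0.50 − 2·arcsin√0.10 = 1.5708 − 0.6435 = 0.9273.

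n per arm = 2·((2.349 + 0.842)/0.9273)² = 23.7, rounded up to 24, so 96 in total. The stated figure is reproduced. Power at 24 per arm = Φ(0.9273·√12 − 2.349) = Φ(0.863) = 80.6%.

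**3. Illustration of crediting such women.** The article gives neither the share prescribed additional medication nor the share of those who would then meet both criteria, so both are assumed. The added successes are taken to be women who would otherwise have failed. A 10% share of whom 25% respond adds 0.10 × 0.25 = 2.5 points. A 20% share of whom 50% respond adds 0.20 × 0.50 = 10 points. An intermediate case is 20% × 30% = 6 points.

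Power = Φ(h·√12 − 2.349), with the active arm held at 50%:

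| Comparator v active | h | h·√12 − 2.349 | Power |
|---|---|---|---|
| 10% v 50% (as planned) | 0.927 | 0.863 | 80.6% |
| 12.5% v 50% | 0.848 | 0.589 | 72.2% |
| 16% v 50% | 0.748 | 0.241 | 59.5% |
| 20% v 50% | 0.644 | −0.120 | 45.2% |

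**4. If active-arm women are credited too.** At 16% v 53%, h = 0.808 and power is Φ(0.449) = 67%, against 60% above. At 20% v 55%, h = 0.744 and power is Φ(0.227) = 59%, against 45%. The loss is smaller in both cases.

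**The case against.** The strongest reply is that the failure rule is an override: a woman given another ELPV drug is a failure, and everyone else is judged on the two criteria. On that reading only a cross-reference is missing, and the full protocol or SAP, neither of which is shown, may supply it. Likewise, a woman who has failed by rule needs no component imputed. This is a plausible reading and may be what was intended. It is stated nowhere, however. The outcome section presents its two criteria as enough for success, and the imputation rule has no exception. A conflict between stated rules remains; it is more than omitted detail.

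The objection to the power figures also stands in part. They rest on assumed rates, and they arise only if the failure rule is set aside. If fewer than 40 women are recruited in 12 months, the article drops significance testing and multiple imputation, and both arguments fall away. The efficacy summaries would still be reported, and the success proportion in them would still need one definition.

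A reader might infer three stronger things that the article does not support.

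- **That an unblinded analyst could pick the coding late.** Randomisation and blinding says the trial statistician is blinded until the final analysis.
- **That the open-ended trial period lets treatment changes after month 6 alter the primary result.** The clause "otherwise an alternative approach will be chosen by the treating clinician" applies after the 6-month visit, when the endpoint has already been assessed.
- **That the abstract's secondary outcome "9) Discontinuation of medications due to treatment failure" is part of this conflict.** It is indeed absent from the secondary outcome list, but that is a separate discrepancy about a secondary outcome and does not show two codings of the primary one.

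**Conclusion.** The concern holds as an unresolved conflict in how the primary endpoint is coded. It affects women prescribed additional ELPV medication before the 6-month assessment who meet both success criteria or have missing assessments. Their number cannot be derived from the article.

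Under the assumed rates, with the active arm at 50%, 24 per arm and the Dunnett-arcsine method, crediting them lowers per-comparison power from about 81% to between 72% and 45%. This is an illustration of sensitivity and not an estimate of what will happen. The stated sample size of 96 is reproduced and is not in question.

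**What to change.** Reconcile Intervention regimens, Primary clinical outcome measure and Statistical analysis into one outcome coding, fixed before unblinding. If the existing failure rule stands, two sentences are enough:

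- In the outcome definition: success also requires that no additional ELPV medication was prescribed between randomisation and the 6-month assessment.
- In the missing-data rule: women who meet that failure condition are coded as non-success and are not imputed.

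If the sponsor intends otherwise, the failure statement under Intervention regimens should be reworded to match. Either way this concerns coding only and changes nothing about what may be prescribed. The cost is small, because the treatment log in Table 1 already records prescriptions given at follow-up visits.

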### Outcomes

#### Feasibility outcomes

After the end of the internal pilot phase feasibility outcomes will be reported:

The feasibility primary outcome is to establish the proportion of eligible patients willing to be randomised to systemic treatment.

The feasibility secondary outcomes are:i).To establish participants’ adherence to treatment regimens;ii).To assess the quality of photographs obtained and suitability for blinded clinical assessment of disease severity;iii).To assess the suitability and completion of paper-based case report forms;iv).To trial a four-armed study design in this population and assess what implications using multiple arms has on recruitment and overall study conduct including post-randomisation dropouts;v).To evaluate the suitability of the chosen clinical outcomes for evaluating treatment response in ELPV.

### Clinical outcomes

#### Primary clinical outcome measure

The primary outcome of the ‘hELP’ study is the *proportion of patients achieving treatment success at 6 months*. Treatment will be classed as successful if *both* patient and investigator success criteria are met:Patient Global Assessment of disease severity of ‘none’ or ‘mild’ (on a 4-point scale of none, mild, moderate or severe disease)Any improvement from baseline judged by blinded assessment of clinical photographs

The composite outcome incorporates both blinded assessment of physical signs, where blinding is important in open-label trials, and patient assessment of symptoms, which is important because physical signs do not always reflect symptoms.

#### Secondary clinical outcome measures

Secondary outcomes comprise the following:i).Reduction in soreness from baseline at 6 months assessed using a 10-point score (0 = no soreness, 10 = most soreness);ii).Disease severity assessed individually by: a) Patient Global Assessment at baseline, 3, 6 and 12 months, b) Investigator assessment by treating clinician at baseline, 3 and 6 months, c) Investigator assessment by blinded assessor using clinical images at baseline and 6 months;iii).Investigator assessment of severity of oral and vaginal sites if affected at baseline, 3 and 6 months;iv).Psychological assessment using the Hospital Anxiety and Depression Scale at baseline and 6 months;v).Sexual function questionnaire at baseline 6 and 12 months;vi).Health-related quality of life using ‘Skindex-29’ and ‘Short Form 36’ questionnaires at baseline and 6 months;vii).Days of topical steroid use (as a marker of disease control in each of the groups);viii).Overall treatment satisfaction;ix).Economic evaluation, which will calculate the average cost of intervention in each treatment group per participant based on prescribed medication.

